# Adapting an Efficacious Peer-Delivered Physical Activity Program for Survivors of Breast Cancer for Web Platform Delivery: Protocol for a 2-Phase Study

**DOI:** 10.2196/52494

**Published:** 2024-06-19

**Keywords:** physical activity adoption, web platform, breast cancer survivors, design, implementation, cost-effectiveness, mobile phone

## Abstract

**Background:**

Interventions promoting physical activity (PA) among survivors of cancer improve their functioning, reduce fatigue, and offer other benefits in cancer recovery and risk reduction for future cancer. There is a need for interventions that can be implemented on a wider scale than that is possible in research settings. We have previously demonstrated that a 3-month peer-delivered PA program (Moving Forward Together [MFT]) significantly increased the moderate to vigorous PA (MVPA) of survivors of breast cancer.

**Objective:**

Our goal is to scale up the MFT program by adapting an existing peer mentoring web platform, Mentor1to1. InquistHealth’s web platform (Mentor1to1) has demonstrated efficacy in peer mentoring for chronic disease management. We will partner with InquisitHealth to adapt their web platform for MFT. The adaptation will allow for automating key resource-intensive components such as matching survivors with a coach via the web-based peer mentoring platform and collecting key indexes to prepare for large-scale implementation. The aim is to streamline intervention delivery, assure fidelity, and improve survivor outcomes.

**Methods:**

In phase 1 of this 2-phase study, we will interview 4 peer mentors or coaches with experience in delivering MFT and use their feedback to create Mentor1to1 web platform adapted for MFT (webMFT). Next, another 4 coaches will participate in rapid, iterative user-centered testing of webMFT. In phase 2, we will conduct a randomized controlled trial by recruiting and training 10 to 12 coaches from cancer organizations to deliver webMFT to 56 survivors of breast cancer, who will be assigned to receive either webMFT or MVPA tracking (control) for 3 months. We will assess effectiveness with survivors’ accelerometer-measured MVPA and self-reported psychosocial well-being at baseline and 3 months. We will assess implementation outcomes, including acceptability, feasibility, and program costs from the perspective of survivors, coaches, and collaborating organizations, as guided by the expanded Reach, Effectiveness, Adoption, Implementation, Maintenance (RE-AIM) framework.

**Results:**

As of September 2023, phase 1 of the study was completed, and 61 survivors were enrolled in phase 2. Using newer technologies for enhanced intervention delivery, program management, and automated data collection has the exciting promise of facilitating effective implementation by organizations with limited resources. Adapting evidence-based MFT to a customized web platform and collecting data at multiple levels (coaches, survivors, and organizations) along with costs will provide a strong foundation for a robust multisite implementation trial to increase MVPA and its benefits among many more survivors of breast cancer.

**Conclusions:**

The quantitative and qualitative data collected from survivors of cancer, coaches, and organizations will be analyzed to inform a future larger-scale trial of peer mentoring for PA delivered by cancer care organizations to survivors.

**Trial Registration:**

ClinicalTrials.gov NCT05409664; https://clinicaltrials.gov/study/NCT05409664

**International Registered Report Identifier (IRRID):**

DERR1-10.2196/52494

## Introduction

### Background

The 5-year survival rates for female survivors of breast cancer have increased from 63% in the 1960s to 90% currently, with >3.6 million survivors of breast cancer in the United States today [1]. There is a large body of evidence on the benefits of aerobic exercise to alleviate sequelae of cancer treatments when conducted with onsite supervision, as well as home-based programs [2-6]. Hence, the American College of Sports Medicine [7] and the American Cancer Society (ACS) [8] recommend that survivors participate in aerobic exercise at moderate to vigorous intensity for at least 150 minutes per week. However, only 24% to 44% of survivors meet these guidelines [8].

The literature suggests that leveraging peer support may help improve moderate to vigorous physical activity (MVPA) adoption among survivors of breast cancer [9]. Sociocultural and communication theories suggest that people are more receptive to assistance when it is delivered by someone perceived as similar to oneself (eg, of comparable age and life experiences) [10]. Peer support for health is used to maximize impact, sustainability, and scale-up of successful interventions while facing limited resources and contextual constraints. With the growing evidence of the key role that physical activity (PA) can play in cancer recovery, we are one of the first teams to extend these research findings into the “real world” by training community volunteers to encourage survivors to adopt MVPA [11-13].

We chose to test the dissemination potential at the ACS, a not-for-profit community-based organization. Specifically, ACS’ Reach to Recovery peer mentors provide emotional support and information to patients with cancer. Hence, it was a “natural fit” to test the effects of these peer coaches encouraging sedentary survivors to become more physically active to enhance their recovery from cancer treatment. Our prior randomized controlled trial (RCT) showed that this peer-delivered intervention (Moving Forward Together [MFT]) was effective in increasing survivors’ MVPA [12]. Coaches who were trained and supervised to provide MVPA counseling via telephone calls to other survivors of breast cancer effectively helped them significantly increase their MVPA to a mean of 129 minutes per week at 12 weeks (*P*<.05).

The telephone counseling component of our evidence-based MVPA intervention is based on the Transtheoretical Model (TTM) [14,15] and Social Cognitive Theory (SCT) [16] of behavior change that have been applied to exercise behavior. Key constructs from the TTM (motivational readiness) and SCT (self-efficacy and beliefs about the importance of MVPA in reducing fatigue etc) underlie the telephone counseling that coaches delivered to survivors in our prior work [12]. We plan to extend these individual-level theories with frameworks from the field of dissemination and implementation science to assess contextual and organizational-level factors that are critical to planning for large-scale implementation of our evidence-based intervention. We will use the expanded Reach, Effectiveness, Adoption, Implementation, Maintenance (RE-AIM) framework of implementation outcome dimensions that includes a model of key contextual determinants of successful implementation, that is, the Practical, Robust Implementation and Sustainability Model (PRISM) [17,18]. RE-AIM has been in use since 1999 and has been applied widely to plan and evaluate the translation of many interventions in primary care and community settings, including smoking cessation interventions, diabetes management, and MVPA promotion [19,20]). As PRISM operationalizes the organizational staff and survivor domains that influence implementation success, we will use PRISM to identify contextual and organizational factors that influence RE-AIM outcomes [18].

### Objective

To address the gap in the literature of limited real-world translation of MVPA promotion among survivors of cancer, our study objective is to develop and test the implementation of Mentor1to1 web platform adapted for MFT (webMFT) as a scalable intervention to effectively increase MVPA among survivors of breast cancer. The study has 2 phases: phase 1, which includes aims 1 and 2, and phase 2 which includes aim 3.

#### Phase 1

In phase 1, we will work with peer coaches who have prior experience in delivering MFT to adapt an existing web platform, Mentor1to1 developed by InquisitHealth Inc (a technology company that offers peer mentoring for chronic disease management via a web platform). In aim 1, we will conduct semistructured interviews with 3 to 4 peer coaches who have already delivered MFT in our prior work to obtain their feedback on how to adapt Mentor1to1 for MFT. In aim 2, we will use the interview data and use rapid, iterative user-centered design principles with another 3 to 4 peer coaches (with prior experience with MFT) to create webMFT.

#### Phase 2

For phase 2, the study aims are as follows:

Aim 3a: conduct an RCT wherein 10 to 12 peer coaches will be trained to deliver webMFT to 56 survivors of breast cancer, who will be randomly assigned to receive either webMFT or MVPA tracking. We will collect quantitative and qualitative data on the acceptability and feasibility of webMFT (eg, number and duration of calls delivered and barriers experienced) and suggestions for improvement from the coaches.Aim 3b: obtain data on survivor outcomes at 12 weeks from accelerometer-measured MVPA (primary outcome) and self-reported quality of life (QOL), physical functioning, mood, and fatigue to help estimate effect sizes for a larger trial to test the impact of webMFT versus MVPA tracking on survivor effectiveness outcomes. We expect that at the postintervention time point, survivors randomized to webMFT will increase MVPA; improve QOL, physical functioning and mood; and decrease fatigue significantly more than survivors randomized to MVPA tracking.Aim 3c: assess organizational-level factors (eg, the barriers and facilitators for implementation, setting and contextual factors, resources required, and alignment of webMFT with workflow and mission) using the RE-AIM and PRISM models [18] by interviewing key multilevel stakeholders at the collaborating organizations.Aim 3d: collect detailed cost, time, and resource information to conduct cost-effectiveness analyses from the perspectives of the survivors, coaches, and cancer care organizations.Aim 3e: develop a guide on how to recruit and build collaborations with other organizations that offer peer mentor programs with which webMFT can be integrated. The long-term goal of this work is to use these data to inform a robust, large-scale pragmatic trial with several cancer care organizations to deliver webMFT to survivors of breast cancer across the country.

## Methods

### Study Design

The study will consist of 2 phases: phase 1 will involve the adaptation and user-centered testing of Mentor1to1 for MFT. We will recruit coaches from past studies who have previously delivered the MFT program. These coaches have experience with intervention content and delivery and thus will be able to provide informed feedback. In phase 2, we will test webMFT using a randomized controlled design.

### Phase 1

#### Recruitment of Coaches

Peer mentors who participated as coaches for the MFT program in a prior RCT [13] will be invited to participate. The eligibility criteria are that the participants must: (1) be aged ≥21 years, (2) currently have an email address and telephone access, and (c) have access to a tablet or computer with internet. We anticipate recruiting 6 to 8 coaches.

#### Adaptation of the Web Platform (Mentor1to1) for MFT

This includes (1) customizing coach-survivor matching criteria; (2) defining the MFT program path in terms of call frequency and counseling content; (3) counseling questions that coaches will ask survivors during each call; (4) counseling questions to structure data entry for coaches via the web platform, and (5) integration of a Fitbit tracker (Fitbit Inc) to autocapture MVPA, heart rate, and step data. The coach-survivor’s matching criteria, progression in the 12-week program, counseling content, and review of the survivor’s weekly MVPA data are based on our prior studies [12,13] and interview data collected during the principal investigator’s participation in the National Cancer Institute’s Speeding Research-Tested Interventions program.

The steps involved in the development process is as follows: the web platform will be rapidly and iteratively tested by (1) InquisitHealth’s team to ensure navigational ease and functionality robustness and (2) our research team to ensure accuracy regarding our design intentions and completeness and fidelity to the content and process of MVPA counseling within MFT. (3) InquisitHealth will conduct interviews via Zoom with 3 to 4 coaches who will complete usability tasks (eg, creating an account in webMFT). (4) After incorporating all available feedback, an additional 3 to 4 coaches (with prior MFT experience) will review the entire system and provide qualitative and quantitative feedback. Quantitative feedback will include the System Usability Scale, which consists of 10 items where coaches will rate the usability of webMFT using a Likert scale (1=strongly disagree; 5=strongly agree) [21]. System Usability Scale has been shown to be reliable and valid. On the basis of recommendations from the coaches, the InquisitHealth team will refine webMFT. Hence, we will adhere to well-established iterative user-centered design principles in adapting Mentor1to1 for evidence-based MFT [22-24]. Coaches will receive a US $100 gift card for their participation.

### Phase 2

Phase 2 will be an RCT of webMFT wherein 10 to 12 coaches (naive to the MFT program, across the collaborating cancer care organizations that have peer mentoring programs) will be trained to deliver webMFT to survivors of breast cancer. We will recruit 56 survivors of breast cancer and randomize them to webMFT (assigned a coach to deliver intervention via the web platform) or an MVPA tracking group (independent MVPA tracking; refer to Figure 1). We will use multiple methods to examine the acceptability and feasibility of the coaches using webMFT and to gather data on the implementation and effects of webMFT on survivors’ MVPA (primary outcome), mood, QOL, physical functioning, and fatigue at baseline and 12 weeks. Finally, we will conduct individual interviews with multilevel stakeholders at the collaborating organizations to collect data, based on RE-AIM outcome dimensions and PRISM domains, to guide the implementation of webMFT on a larger scale.

**Figure 1 figure1:**
[figure not shown]
Study design (phase 2). MVPA: moderate to vigorous physical activity; webMFT: Mentor1to1 web platform adapted for Moving Forward Together.

### Description of webMFT

Mentor1to1 is a web-based platform for coach and survivor enrollment; survivor-to-coach matching; one-on-one remote coach mentoring via phone, text, and smartphone messaging; automated MVPA tracking via Fitbit; and administrator oversight and support. Access to the system by both the coach and staff is password protected. Within the webMFT, the coach will be able to review information from prior calls (eg, a survivor’s MVPA recorded by a Fitbit activity tracker) and review information for the upcoming call (eg, counseling questions). When ready for a call to a webMFT participant, the coach will click a button on the computer to initiate the call. The system calls the survivor and connects the coach and survivor for a one-on-one telephone conversation. This avoids the need to exchange contact information. All calls are generated from a secure server, allowing the tracking of call frequency, length, and recording for quality control, safety, and training purposes, while respecting Health Insurance Portability and Accountability Act (HIPAA)–mandated security and privacy requirements. During the call, coaches will be expected to document their discussion for each specified counseling question; additional notes can be taken throughout the call within the platform. At the end of each call, coaches will collaboratively set MVPA goals with the participants, discuss strategies to achieve those goals in the upcoming week, and schedule the next call. As needed, the platform will assist with scheduling time zone differences between the coach and the participant. The system will send email or text reminders to the coach and the participant about their upcoming call.

### Recruitment of Coaches

We will work with cancer care organizations (eg, Cancer Hope Network and Pink Lemonade Project) to recruit coaches and survivors. In total, we will recruit 10 to 12 coaches across the organizations to be trained to deliver webMFT. Each coach will be asked to work with 4 to 5 survivors over the study duration. As in our prior work [12,13], the organizations will mail or email informational letters and brochures to peer mentors, offering them the opportunity to become a coach and receive training in the delivery of webMFT.

Eligibility criteria for coaches include that they must (1) be a current peer mentor (at least 1 year) at the organization; (2) have an email address, telephone access, and access to a tablet or computer with internet to use the web platform; (3) be willing to participate in group training via videoconference; (4) be willing to have calls recorded and reviewed; (5) be willing to be supervised; (6) have a baseline level of digital literacy for this health technology (ie, sufficient internet speed and proficient in typing); and (7) currently exercise for at least 60 minutes per week.

### Survivor Recruitment

The collaborating cancer care organizations will be asked to send informational mailings or emails about the study to their lists consisting of survivors of breast cancer. Other recruitment avenues will include informational mailings from oncology practices, tumor registries, and community events. Interested survivors will be asked to contact the study’s research assistant who will explain the study and obtain verbal informed consent to conduct a telephone screen for eligibility. If eligible, the staff will send the survivor an informed consent document through REDCap (Research Electronic Data Capture; Vanderbilt University) [25,26]; once signed, participants will be sent a copy for their records. Participants will be mailed a physician consent form for their participation in the study. After the consent forms are obtained, all survivors will be mailed an Actigraph (GT3X; Actigraph LLC) accelerometer to monitor MVPA with instructions and a stamped envelope to return the Actigraph. In addition, they will receive instructions on completing baseline questionnaires within REDCap. After the baseline assessments are completed and the Actigraph has been reviewed for wear time and confirmation of a sedentary lifestyle, participants will be mailed a Fitbit Inspire 2 tracker. Participants will also receive a Fitbit manual and a study username and password to log in to the Fitbit app on their phone. Survivors randomized to the MVPA tracking arm will receive an identical Fitbit in the mail; their data will be tracked directly via the Fitbit Application Programming Interface.

Eligibility criteria for survivors include the following: (1) women aged >21 years; (2) diagnosis in the past 5 years with stage 0 to stage 3 breast cancer (completed surgery, radiation, or chemotherapy, and those currently receiving hormone therapy; physician consent for all study survivors will be obtained); (3) ability to read and speak English; (4) those with sedentary lifestyle (ie, <30 minutes per week of vigorous exercise or <90 minutes per week of moderate intensity exercise for the past 6 months); (5) ability to walk unassisted; and (6) access to a smartphone with Bluetooth and internet access. Women with more advanced disease (stage 4) and medical or psychiatric problems (eg, coronary artery disease, peripheral vascular disease, diabetes, and orthopedic problems) that may interfere with protocol adherence will not be included. These inclusion and exclusion criteria are similar to those used in our prior work [12,13]. Survivors will be asked to provide consent for medical chart review to extract disease and treatment history.

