### Sample Size

Power calculations were based on data from our prior work with MFT [27], and data from the study by Cadmus-Bertram et al [28], who compared web-based tracking+Fitbit to pedometer alone among postmenopausal women. Comparing the effects of coach counseling [27] to web-based tracking+Fitbit [28] on changes from baseline in MVPA would yield a medium effect size, *d*=0.60. Assuming similar effect sizes and a 2-sided α=.05, we would have more than sufficient power to test intervention effects on changes in MVPA (minutes per week) at the end of intervention with 20 survivors per arm. However, given the risk of powering on pilot studies, we have conservatively inflated the sample size to 25 survivors per arm. On the basis of our prior work, we expect attrition to be ≤10% at 12 weeks, so we will recruit a total of 56 women (n=28 survivors per arm) to obtain complete data from 50 survivors.

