#### Random Assignment

Survivors will be randomly assigned to a group after informed consent and baseline data are obtained. Consistent with prior work, the sample will be stratified for 2 variables that may affect MVPA outcomes (age: <60 years or >60 years; and treatment: received or not received chemotherapy). The randomization scheme will be generated using the R (the R Foundation for Statistical Computing), based on a permuted block randomized procedure with small, random-size blocks so that equal numbers of survivors are randomized to webMFT or MVPA tracking by age and treatment. The project director will contact the survivor and disclose the group assignment from a sealed envelope.

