#### Exercise Counseling

Coaches will be asked to contact survivors using the web platform and make 12 calls (1 call per week over 12 weeks). Each call will take approximately 15 to 20 minutes. The purpose of the calls is to build a supportive relationship with the survivor, assess motivational readiness, review MVPA participation (participant Fitbit data viewed on the web platform), identify any health concerns, assist the survivor to identify relevant barriers to MVPA, and help her to problem solve such barriers and set MVPA goals. In addition, the coach will provide feedback and reinforce and encourage efforts to start being active and stay active. The counseling will be matched to the survivor’s motivational readiness assessed at the start of each call. For example, women in the precontemplation stage will be given information to increase their awareness of the benefits of MVPA after cancer treatments (eg, improved physical functioning). The goal, as in prior work, will be to gradually increase the amount of moderate intensity aerobic exercise that is performed to the current national recommendations of at least 150 minutes of MVPA per week [7]. Coaches will be trained not to provide medical advice but to encourage patients to contact their oncologist for medical care and health issues. If patients report symptoms such as chest pain or difficulty breathing, participation will be temporarily halted, and they will be referred to their oncologist.

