### Data Analyses

#### Overview

We will examine RE-AIM dimensions (Tables 1-3) to guide us in assessing the potential for larger-scale implementation of webMFT. We will conduct descriptive analyses of reach, adoption, and implementation outcomes including acceptability and feasibility of webMFT (eg, the number and mean duration of calls, barriers, and perceived feasibility of intervention delivery as judged by coaches). According to the current recommendations [46], we will consider webMFT feasible if >75% of the scheduled calls are delivered and survivor and coach and acceptability or satisfaction exceed 80% on rating scales (ratings of “moderately” to “very satisfied/acceptable”). Feedback from coaches and survivor debrief interviews will be used to revise and update webMFT for a larger-scale implementation trial.

We will assess potential between-group differences (webMFT vs MVPA tracking) in baseline variables (eg, age and medical history) using graphical methods, nonparametric and parametric tests as appropriate (eg, Wilcoxon rank-sum test for skewed data, 2-tailed *t* tests for normally distributed continuous data, and chi-squared tests for categorical data). Any variables not balanced by randomization will be controlled for as covariates in subsequent analyses, provided they are significantly associated with the outcome under consideration (at a modest *P*<.10 level).

We will assess effectiveness by examining the effects of webMFT versus MVPA tracking on the change in survivors’ MVPA in minutes per week (accelerometer data) at 12 weeks (3 months) using a mixed effects regression model, in which we will regress MVPA at 12 weeks on baseline MVPA, randomized group, wear time, and any variables not balanced by randomization. Models will include random intercepts to adjust for repeated measures within the participant over time. We will use a similar approach to estimate the effects of group on mood, QOL, physical function, and fatigue at 12 weeks. The interest is in estimating effect sizes and CIs. Analyses will be conducted on the intent-to-treat sample with all randomized participants included. Mixed effects models use a likelihood-based approach to estimation and do not require any direct imputation of missing outcomes.

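### The sedentary criterion joins its two limits with *or*, so read literally it admits women already at or above the program's 150-minute goal

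*Protocol article*

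**What the plan says.** Under Survivor Recruitment, inclusion criterion 4 asks for a sedentary lifestyle and then defines it: "<30 minutes per week of vigorous exercise or <90 minutes per week of moderate intensity exercise for the past 6 months". The limits are introduced by *ie*, so they are the definition and not an example.

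The same section adds a later check. The Fitbit is mailed only after the baseline assessments are complete and "the Actigraph has been reviewed for wear time and confirmation of a sedentary lifestyle". No number of minutes is attached to this check. Under Random Assignment, "Survivors will be randomly assigned to a group after informed consent and baseline data are obtained", so the check can act before allocation.

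The Background describes the target of the peer program as sedentary survivors. Exercise Counseling sets the aim of building up gradually to the "current national recommendations of at least 150 minutes of MVPA per week".

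For the primary outcome, the Data Analyses overview says "we will regress MVPA at 12 weeks on baseline MVPA, randomized group, wear time, and any variables not balanced by randomization".

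**The concern.** A woman fails the criterion as written only if she reaches both limits: at least 30 minutes vigorous and at least 90 minutes moderate. High activity in one intensity alone never excludes her. The rule therefore sets no upper bound on total activity, although its label and the program's aim both imply one.

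Two things are at stake. First, women already at goal may have less room to gain, which could shrink the difference between arms. Second, the trial is meant to supply effect sizes for a larger trial. If the enrolled population is a mix of inactive and active women, it is unclear to whom the estimate applies, and the same wording may be carried into the next protocol.

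**Working it through.** **1. The plan's own figure.** Sample Size gives 25 evaluable women per arm and attrition of at most 10%. 25 / 0.90 = 27.8, rounded up to 28 per arm, or 56 in total. This reproduces, and the eligibility wording does not change it.

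**2. Logic of the criterion.** Let V and M be weekly minutes of vigorous and moderate exercise. As written, a woman is eligible if V < 30 or M < 90. If both limits must hold, she is eligible if V < 30 and M < 90.

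| V | M | Total | Eligible under *or* | Eligible under *and* |
|---|---|---|---|---|
| 0 | 150 | 150 | yes | no |
| 0 | 300 | 300 | yes | no |
| 200 | 0 | 200 | yes | no |
| 40 | 100 | 140 | no | no |
| 29 | 89 | 118 | yes | yes |

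Under *and*, total reported exercise is below 30 + 90 = 120 minutes, which is under the 150-minute goal. Under *or* there is no cap. The fourth row shows how the literal rule misfires: it turns away a woman at 140 minutes and admits one at 300.

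**3. Whether another passage corrects it.** The Actigraph review is the only other check on activity. It gives no threshold, and the only definition of a sedentary lifestyle in the article is the *or* wording. It may have removed active women in practice, but the text does not establish that it would.

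**4. What dilution could look like (illustration only).** Sample Size says that coach counseling compared with web-based tracking "on changes from baseline in MVPA would yield a medium effect size", d = 0.60. The test is specified as "Assuming similar effect sizes and a 2-sided α=.05". Suppose a share f of those enrolled is already active and gains nothing, with the SD unchanged. Then d_eff = 0.60 × (1 − f). Power is from the two-sample t test with 25 per arm, noncentrality d_eff × √(25/2) and 48 degrees of freedom.

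| f (assumed) | d_eff | Power |
|---|---|---|
| 0% | 0.60 | 0.547 |
| 10% | 0.54 | 0.465 |
| 20% | 0.48 | 0.383 |
| 30% | 0.42 | 0.307 |
| 40% | 0.36 | 0.239 |

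The starting value of 0.547 follows from the plan's own d, alpha and sample size. It is a separate matter from the eligibility wording. Only the drop from that value would belong to this point, and only if the assumed share and zero gain were true.

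**The case against.** The intent is clear from context. The label, the Background and the program's aim all point to women with low activity, and a woman walking 300 minutes a week does not fit the label. The screening form is not shown, and staff may have required both limits. The Actigraph review comes before randomization, and an operational cut-off is something an article commonly leaves to the full protocol. All of this is fair. It means that nobody can say from the article that active women were enrolled. It does not remove the defect, because the rule is stated in full and says something other than what is intended.

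A reader might go further and infer that the effect is diluted by a definite amount, for instance by applying the 24% to 44% of survivors who meet the guideline according to the Background. The article does not support that. The figure describes survivors in general, not women who have passed a sedentary screen and a device check. Zero gain and an unchanged SD are also assumptions. In addition, Survivor Recruitment says the criteria resemble those of the team's earlier studies, and the coaching part of d = 0.60 comes from earlier work on the program. If the same wording applied there, that part of d may already include such women. The sources are not at hand, so this cannot be settled.

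Nor is there between-arm bias, since any such women would be randomized to both arms. The primary model adjusts for baseline MVPA. That reduces noise, although it would not restore a diluted mean effect.

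**Conclusion.** The point holds as a wrongly stated eligibility rule. Read literally, the criterion admits women at or above 150 minutes per week in a single intensity, which conflicts with the trial's stated population and the program's aim. The Actigraph check is at best a partial safeguard, because no threshold is given for it.

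Dilution of the MVPA effect is a possibility and has not been shown. The documents give no share of such women and no effect by baseline activity, so its size is unknown and the power values above are illustrations. No sample-size figure changes under the correction. The main consequence is for interpretation: the population behind the effect size is not well defined until the authors say how the rule was applied.

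**What to change.** Replace *or* with *and* in criterion 4 and on the screening form, so that both limits must hold. State which reading was used in screening and what MVPA threshold the Actigraph confirmation used.

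The self-report limits should not simply be copied onto the device. They concern exercise over the past 6 months. The Actigraph records movement during waking hours over 7 days, in 10-second epochs scored by cut points (Measures, Effectiveness). Ordinary movement scored as moderate could then exclude women who do no exercise.

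The Results section reports 61 women enrolled by September 2023, against a target of 56, so rewording may affect few women in this trial. Reporting matters more. Give the number admitted only under the *or* reading, by arm, and add a sensitivity analysis of the primary MVPA outcome without them. They can be identified from the screening answers if minutes were recorded by intensity. If not, baseline Actigraph MVPA can be used with a threshold stated in advance. Because the exclusion rests on data from before randomization, it keeps the randomized comparison within the remaining women.

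The cost is small: one word, a few sentences of reporting, somewhat lower precision in the sensitivity analysis, and the exclusion of a few women in any remaining or future recruitment.
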